## 8.3 Recruitment planning

All 20,000 subjects for COVID-RED will be recruited at the start of the study in the first and second quarter of 2021. In section 4.1, the population from which these subjects will be recruited is detailed. Subjects will be followed for up to 3 months during the Learning Phase, 3 months during Period 1, and 3 months during Period 2, for a total of up to 9 months. Subjects entering the study at the end of the recruitment period may directly start with Period 1 and will not be part of the Learning Phase. In Periods 1 and 2, subjects will receive both the control and experimental condition in random order. Recruitment and follow-up will be completely remote and take place via post, email, phone and electronic web portals. In this way, risk of SARS-CoV-2 infection is minimized as much as possible for those wanting to

participate in the trial and for the staff conducting the trial. See Figure 2 for an illustration of the planned recruitment timelines and study procedures.

## **8.4 Study procedures**

In APPENDIX 1, the study procedures for the subjects are summarized for the current protocol. Further details regarding specific procedures are provided below. Figure 4 provides an overview of the subject journey including all potential moments at which subjects can fail to register, drop out and/or fail to follow protocol.

### **8.4.1 (E)mail invitation to participate in COVID-RED**

Subjects will be recruited from existing cohorts from previous studies as well as via public outreach campaigns. Members of existing cohorts will be contacted through email or mail to inform them about the COVID-RED study and to invite them to visit the COVID-RED web portal. For the public campaign, an online URL will be available for any individual who wants to know more about the study and would like to participate.

### **8.4.2 Registration and verification of inclusion/exclusion criteria**

In the COVID-RED web portal, subjects will be asked to register by entering their e-mail address. Subsequently, subjects will fill in a pre-screening survey in which their eligibility for the study will be confirmed. Several additional demographic details will also be asked to characterize the screened population as well as the risk factors. Subjects will be asked if they give permission to the study team to collect and use this data.

### **8.4.3 Informed consent by subject**

After the eligibility verification and confirmation of risk group (normal or high), subjects are provided with further information on the study, and if subjects wish to participate, they must sign the informed consent form. Subjects will be given the chance to contact the study team for any questions they have during this process. In case the stratum for the assigned risk group is full, subjects will be notified they are not able to join the study prior to the consent process.

The full consent process is described in more detail in section 11.2.

#### **8.4.4 Baseline survey**

Subjects will be asked to enter baseline information on socio-demographic characteristics, comorbidities, medication use, COVID-19 vaccination status and COVID-19 risk factors in the COVID-RED web portal.

#### **8.4.5 Assignment of Unique Identification code (UID) and randomization to sequence**

Following the successful signing of informed consent form, subjects will be stratified based on their demographic information provided at registration to either the normal-risk or high-risk group. In addition, they will be assigned a UID and randomized to one of the two sequences. Subjects will be blinded as to the sequence that they have been assigned to.

#### **8.4.6 Receive starter kit**

Subjects will then receive a starter kit through the postal service. This starter kit will contain the following items: Ava bracelet, self-sampling kits for serology tests, detailed instructions on how to use the self-sampling kits, general study instructions for the Ava bracelet and Ava COVID-RED app and pre-addressed (medical) return envelopes with prepaid postage.

#### **8.4.7 Installation of the Ava COVID-RED app, log in and pairing of Ava bracelet**

Subjects will receive their login details along with instructions on how to download the Ava COVID-RED app from the iOS and Android app stores on their smartphone. Subjects will be asked to install the app and log in using their credentials. After logging in, subjects will be able to change their password by navigating to the My Profile part of the Ava COVID-RED app; instructions for how to reset their password will be provided as part of the starter kit. Subjects will need to provide a personal email address within the Ava COVID-RED app to enable password recovery features. The personal email address will not be viewable by trial staff including Ava employees. At first login, subjects will also complete a survey in-app containing basic demographic and epidemiological information which will be necessary for the development and implementation of the algorithms. All subjects will also be instructed to pair the received Ava bracelet with the Ava COVID-RED app prior to wearing it for the first time.

#### **8.4.8 Collection & testing of plasma/blood sample**

Subjects will be asked to self-collect a capillary blood sample using provided materials at Baseline as well as upon completion of the Learning Phase, Period 1 and Period 2 by fingerprick for up to a total of 4 samples during the study. Subjects entering the study at the end of the recruitment Period will have a total of 3 samples, they will be asked to self-collect a sample at Baseline as well as upon completion of the Period 1 and Period 2.

Subjects will be requested to send the sample to the central laboratory within 24 hours using provided, pre-addressed medical envelopes with prepaid postage. The samples will be processed and stored at the central laboratory on the day of receipt. All samples collected at the end of the Learning Phase, and Period 2 will directly be tested for SARS-CoV-2 antibodies using an in-house ELISA method upon receipt. By testing at the end of each stage of the study, we have nearly 100% knowledge of infection status at the end of each trial period, thereby allowing assessment of sensitivity and specificity. Baseline samples will only be analyzed if the sample collected at the end of the Learning Phase is positive for SARS-CoV-2 antibodies or if the subject entered the study at the end of the recruitment Period. Samples collected at the end of Period 1 will only be analyzed if the sample collected at the end of Period 2 is positive for SARS-CoV-2 antibodies. In this way, subjects who had a SARS-CoV-2 infection prior to participation in the study or at start of Period 2 can be identified. The central laboratory in-house ELISA method assesses total SARS-CoV-2 antibodies (Ab), and if positive, isotype-specific (IgM and IgG) SARS-CoV-2 antibodies. Note that anti-S antibody serology tests will be used for baseline and Learning Phase samples. Anti-N antibody serology tests will be used for the Period 1 and Period 2 samples. Subjects will be informed on their testing result for SARS-CoV-2 antibodies.

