### **3.6 Serology testing for SARS-CoV-2**

Subjects will also be asked to donate fingerprick blood for SARS-CoV-2 serology (antibody) testing at baseline, at the end of the Learning Phase (depending on when they entered the study), and at the end of each period to determine if and when (during which period) they became infected with SARS-CoV-2. Baseline samples of subjects will only be analysed if the sample collected at the end of the Learning Phase is positive for SARS-CoV-2 antibodies or if the subject entered the study at the end of the recruitment Period. Samples of subjects collected at the end of Period 1 will only be analysed if the sample collected at the end of Period 2 is positive for SARS-CoV-2 antibodies. Given the likelihood that subjects will be vaccinated during follow-up (see Section 3.7), differentiation between antibodies produced following a COVID-19 vaccination or antibodies produced as a result of a natural infection by the SARS-CoV-2 virus is essential. This is especially important during Period 2 when evaluation of the V2 algorithms takes place. All approved COVID-19 vaccines and likely candidates still being developed or evaluated at the time of writing elicit an immune response against the virus spike (S) protein resulting in antibodies directed against the S-protein. Natural infections elicit an immune response resulting in antibodies against the virus S-protein and Nucleocapsid (N)-protein. Due to logistical limitations in the short term, anti-S antibody serology tests will be used for baseline and Learning Phase samples, while anti-N antibody serology tests will be used for the Period 1 and Period 2 samples.

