### 4.4 Sample size calculation

A crossover design will be used in the current study meaning that subjects will contribute data to both the control and experimental condition. Unlike a traditional crossover study, however, the proposed crossover design includes a missing-data mechanism by design. Subjects with SARS-CoV-2 infection in the Learning Phase will have their data excluded from Period 1 and Period 2. Likewise, subjects with SARS-CoV-2 infection in Period 1 will have their data excluded from Period 2. This prevents the application of standard statistical adjustments due to missing-data. A bootstrap approach will be used to conduct statistical testing which accounts for this missing data mechanism in those cases when both periods are taken into account in the analysis. For more details, refer to Section 10 (Statistical analysis). With analyses based on bootstrap methods, classical power calculations are not possible. However, we can gain an indication of the bounds on power that can be expected. Additionally, power is highly dependent on the infection rate in the Netherlands during the conduct of the trial and for which we expect continued volatility, therefore we present power approximations based on the data reported by the RIVM on the number of individuals tested and found positive for SARS-CoV-2 infection in Weeks 36 through 40 of 2020, see Table 2.

*Table 2: Number of individuals tested in the Netherlands and amount of positive tests as reported by RIVM in Weeks 36 through 40 of 2020*

|                           | Week 36 | Week 37 | Week 38 | Week 39 | Week 40 |
|---------------------------|---------|---------|---------|---------|---------|
| Individuals Tested | 180,182 | 191,204 | 206,670 | 207,670 | 223,274 |
| Positive tests     | 5,427   | 7,640   | 12,217  | 16,602  | 23,264  |

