#### 4.4.1 Ever-infected analysis

For the first analysis that will be performed for the primary analysis, log-linear modelling will be used. As an approximation, we will use the power calculation of a Fisher exact test. We provide power estimates based upon 10,000 subjects per arm as will approximately be

available within Period 2. In Table 3 and Table 4 both scenarios are presented given different assumed infection rates in the Netherlands and for various differences in sensitivity (Table 3) and specificity (Table 4) to be detected. From these assessments of the trial power, we see that the most recent RIVM data lead to sufficient power for differences in sensitivity of at least 5.5%. We also see that the trial is well powered for very small changes in specificity with sufficient power for differences of at least 1.5%.

*Table 3: Trial power for a Fisher exact test to detect differences in sensitivity based on infections rates of Weeks 36 through 40 of 2020*

|                                | Week 36 | Week 37 | Week 38 | Week 39 | Week 40 |
|--------------------------------|---------|---------|---------|---------|---------|
|                                | 10,000  | 10,000  | 10,000  | 10,000  | 10,000  |
| Difference in Sensitivity 1%   | 0.03    | 0.03    | 0.04    | 0.04    | 0.05    |
| Difference in Sensitivity 2.5% | 0.03    | 0.05    | 0.07    | 0.09    | 0.13    |
| Difference in Sensitivity 4%   | 0.06    | 0.1     | 0.16    | 0.23    | 0.33    |
| Difference in Sensitivity 5.5% | 0.1     | 0.18    | 0.31    | 0.45    | 0.62    |
| Difference in Sensitivity 7%   | 0.18    | 0.32    | 0.55    | 0.72    | 0.88    |

Table 4: Trial power for a Fisher exact test to detect differences in sensitivity based on infection rates of Weeks 36 through 40 of 2020

|                                 | Week 36 | Week 37 | Week 38 | Week 39 | Week 40 |
|---------------------------------|---------|---------|---------|---------|---------|
|                                 | 10,000  | 10,000  | 10,000  | 10,000  | 10,000  |
| Difference in Specificity -3%   | 1       | 1       | 1       | 1       | 1       |
| Difference in Specificity -1.5% | 0.79    | 0.78    | 0.75    | 0.76    | 0.73    |
| Difference in Specificity 1.5%  | 0.82    | 0.79    | 0.77    | 0.76    | 0.76    |
| Difference in Specificity 3%    | 1       | 1       | 1       | 1       | 1       |

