### *General statistical approach*

Appropriate statistical methods will be selected for each research question depending upon the nature of the data distribution as well as the effect that is to be characterized. Categorical variables will be presented as absolute numbers and percentages, while continuous variables will be described by number of observations, mean, standard deviation, median and range (minimum and maximum). While maximum effort will be put into the minimization of missing data, the remote nature of the study and the reliance on self-reporting by the subjects might lead to the presence of missing data. Where necessary, missing data mechanisms will be investigated and imputation methods will be used or robust statistical methods such as bootstrap estimation employed. The count and percentage of known missing data will be described. Analyses and results between and within the study conditions will also be reported overall and separately for the different strata (e.g., normal-risk vs. high-risk population). Additionally, with the exception of the baseline data, all data will be analysed and reported within each period of the trial with pooling of the data only in specifically mentioned cases in the sections below. All statistical confidence intervals will be two-sided and at the 95% level. P-values, or similar measures resulting from bootstrap methods, will be considered significant if less than 0.05 with two-sided testing and if less than 0.025 with one-sided testing. No adjustments for multiplicity of tests are planned. For both the primary and secondary endpoints (where relevant), we will assess the COVID-19 vaccinated portion of the study sample as a key subset. The potential effect of COVID-19 vaccination among some subjects on the analyses of interest will be investigated using sensitivity analyses. This may include truncation of certain data occurring after vaccination events as part of these sensitivity analyses. Further details will be captured in the statistical analysis plan.

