### 10.2 Primary Analysis of Primary Endpoint(s)

The primary analysis of the primary endpoint will compare the performance of the algorithm applied in each study condition to detect if subjects were ever infected during Period 2. This analysis will be performed on both the Intention-to-treat and Efficacy analysis sets, within each period and stratified per risk group. For the subjects within each study condition, the daily prediction of possible SARS-CoV-2 infection and the results of PCR/antigen and serology tests will be summarized over the whole period per subject to determine (1) if a subject was ever judged to have a high risk for a potential SARS-Cov-2 infection (i.e. received a red-light indicator from the Ava COVID-RED app), and (2) if a subject was ever confirmed to have a SARS-CoV-2 infection by PCR/antigen or serology testing. For this comparison, parameters such as sensitivity, specificity, positive predictive value, and negative predictive value will be calculated.

To confirm whether a subject was ever infected in Period 2 with SARS-CoV-2, the serology status at the end of Period 2 for each subject still alive at that time will be used as the gold standard. Those with a previous positive test result will be excluded from the analysis. For subjects not alive at the end of Period 2, the status of available SARS-CoV-2 virus tests during Period 2 will be used (positive at any time) and for those without any test results, a physician diagnosis during Period 2 will be accepted provided there was a supportive lung CT scan used. All other subjects will be summarized for transparency but excluded from the estimation for sensitivity, specificity, positive predictive value and negative predictive value.

The following quantities are needed for these statistics:

- **Predicted condition positive:** The total number of subjects that obtained a red-light indicator from the Ava COVID-RED app at least once during Period 2.
- **Predicted condition negative:** The total number of subjects that never obtained a red-light indicator from the Ava COVID-RED app during Period 2.
- **Condition positive:** The total number of subjects who tested positive at least once using SARS-CoV-2 virus testing during Period 2 OR who had a positive serology test at the end of Period 2.
- **Condition negative:** The total number of subjects who never tested positive for the SARS-CoV-2 virus during Period 2 AND who had a negative serology test at the end of Period 2.

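### One unconfirmed anti-N result at the end of Period 2 defines an infection, and no stated assay accuracy supports the claim of near-complete knowledge of infection status

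*Protocol*

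**What the plan says.** Section 10.2 takes serology at the end of Period 2 as the gold standard for every subject still alive. A subject is condition positive after any positive virus test in Period 2 "OR who had a positive serology test at the end of Period 2". No second result is needed. Subjects with an earlier positive result are excluded.

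Section 8.4.8 describes the assay: "The central laboratory in-house ELISA method assesses total SARS-CoV-2 antibodies (Ab), and if positive, isotype-specific (IgM and IgG) SARS-CoV-2 antibodies". It gives no accuracy figures and does not say how the total and isotype results combine into a reported positive. It also says that "we have nearly 100% knowledge of infection status at the end of each trial period, thereby allowing assessment of sensitivity and specificity", and the only ground offered is that a sample is taken at the end of each stage.

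Section 3.6 fixes which antigen is read when: "anti-S antibody serology tests will be used for baseline and Learning Phase samples, while anti-N antibody serology tests will be used". The anti-N reading applies to what is collected when each of the two crossover periods ends. The Period 1 sample is analysed only if the Period 2 sample is positive.

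**The concern.** The reference standard is handled as if it had no error. Roughly 10,000 people per condition are screened and few are expected to be infected, so even a very specific assay can produce false positives that are not negligible beside the true infections. A falsely positive subject has no reason to get a red light beyond the background rate. Each one therefore pulls measured sensitivity towards that rate in both conditions and shrinks the difference between them. A real benefit of the bracelet could be missed.

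Period 1 has a separate gap. Someone whose serum always reacts in the anti-N assay has an entry sample read only with anti-S. That person can look negative at entry and positive at the end of Period 1, and so count as a Period 1 infection.

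**Working it through.** **Reproducing Table 3.** Stated inputs: 10,000 per arm and a Fisher exact test (Section 4.4.1), two-sided 0.05 (Section 10), and weekly national positives of 5,427 to 23,264 (Table 2). The protocol states neither the control sensitivity nor the number infected per arm, so both were fitted, with infections proportional to the weekly positives. Control sensitivity 0.90 with 58/82/131/178/250 infected per arm reproduces all 25 cells to within 0.01. For a 7-point difference it gives 0.18 in Week 36 and 0.88 in Week 40, as printed. The other values tried fit worse: 0.85 matches 19 cells, 0.88 matches 22, and 0.92 at most 18. Using test positivity (3.0% to 10.4%) as the infection rate does not fit, because Week 36 power at 7 points would be at least 0.41. The implied infected share is 0.58% to 2.5%.

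**Assumptions for the dilution.**
- Assay specificity *c* is not given; it is varied from 99.9% to 99%.
- No infection is missed, since virus tests also count.
- The red-light rate in uninfected subjects is 0.20, because the Table 4 powers imply an algorithm specificity of about 0.8.
- True sensitivity is 0.90 (control) against 0.97 (experimental).

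**Formulas**, with *I* infected per 10,000:
- false positives *F* = (10,000 − *I*)(1 − *c*)
- true share *T* = *I*/(*I* + *F*)
- apparent sensitivity = *T* × true sensitivity + (1 − *T*) × 0.20
- power by the two-proportion normal approximation with *n* = *I* + *F* per arm (0.89 with no error, against 0.88 for the exact test)

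**Example, *I* = 250, *c* = 99%.** *F* = 9,750 × 0.01 = 97.5 and *T* = 250/347.5 = 0.719. Control reads 0.719 × 0.90 + 0.281 × 0.20 = 0.704. Experimental reads 0.719 × 0.97 + 0.281 × 0.20 = 0.754. The difference is 5.0 points and power is 0.32.

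| Assay specificity | False positives | Share false | 0.90 reads | 7 points reads | Power | Power if half of *F* is removed |
|---|---|---|---|---|---|---|
| 100% | 0 | 0% | 0.90 | 7.0 | 0.89 | 0.89 |
| 99.9% | 10 | 4% | 0.87 | 6.7 | 0.76 | 0.82 |
| 99.8% | 20 | 7% | 0.85 | 6.5 | 0.65 | 0.76 |
| 99.5% | 49 | 16% | 0.79 | 5.9 | 0.45 | 0.60 |
| 99% | 98 | 28% | 0.70 | 5.0 | 0.32 | 0.45 |

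The last column assumes that the check of the Period 1 sample removes half of the false positives. That fraction is an assumption.

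**Other infection rates, no removal, same four specificities.**
- At 58 infected, 15/26/46/63% of condition positives are false and 0.90 reads 0.80/0.72/0.58/0.46.
- At 500 infected, as in the worked example of Section 10.4.2, 2/4/9/16% are false.

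**Specificity needed.** For 95% of condition positives to be true without confirmation, *c* must be at least 1 − *I*(0.05/0.95)/(10,000 − *I*). That is 99.87% at 250 infected and 99.97% at 58.

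**Other measures** (250 infected, control condition, *c* = 99%). Algorithm specificity stays at (9,652.5 × 0.80)/9,652.5 = 0.80. PPV rises from 225/(225 + 1,950) = 10.3% to (225 + 19.5)/2,175 = 11.2%.

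**The case against.** The strongest reply is that the protocol already has a safeguard. Every positive Period 2 sample triggers an anti-N reading of the Period 1 sample, and earlier positives are excluded, so a persistent cross-reactor with a Period 1 sample leaves the primary Period 2 analysis. This stands, and it is why the last column of the table matters. It does not catch a false positive that first appears at the end of Period 2. The subjects it removes are also not lost: two positive anti-N samples with an anti-S entry reading make them Period 1 infections. Sections 10.2 and 10.4 analyse Period 1 and pool it with Period 2. The primary comparison is in Period 2, so this second effect is peripheral to it.

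Three further points stand.
- The sentence in Section 8.4.8 can be read as being about coverage only.
- The low infection rate is back-solved, not stated. Section 10.4.2 uses 500 and 600 as an illustration, where the dilution is smaller.
- The dilution acts in both conditions, so it tends to hide a benefit, not create one.

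Section 10 defers sensitivity analyses to the SAP, so their absence from the protocol is not itself the fault. The fault is the classification rule and the sentence, both of which the protocol fixes.

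A reader might infer that the protocol's claim is shown to be false, or that the plan itself expects 0.6% to 2.5% infected. The documents support neither. Assay specificity is unknown, and at 99.9% with 250 infected about 96% of condition positives are true. A reader might also infer that the laboratory's isotype result is discarded; the protocol only leaves its role unstated.

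**Conclusion.** The point holds as one of missing support. A single positive end-of-Period-2 result is enough, no assay accuracy is stated, and the confidence expressed in Section 8.4.8 rests on sampling coverage. At the infection rates that reproduce Table 3, modest assay error lowers measured sensitivity, shifts PPV and costs power, while algorithm specificity is barely touched.

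The loss ranges from slight to severe: with 250 infected, power for a 7-point difference falls from 0.89 to between 0.82 (specificity 99.9%, half of the false positives removed) and 0.32 (99%, none removed). This rests on the fitted control sensitivity of 0.90, the 0.20 red-light rate, no missed infections and the assumed specificity range. It should be fixed, but it does not invalidate the design or create a spurious benefit.

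**What to change.** 1. In Section 10.2, or by reference to the SAP, add two analyses. The first corrects sensitivity, specificity, PPV and NPV for the laboratory's validated assay sensitivity and specificity, which should be stated. The second counts a positive serology result only when a positive virus test, or an independent second assay on the stored sample, supports it. The reflex isotype result should serve as support only if the laboratory shows that it adds specificity, because it belongs to the same in-house method. If the second assay is independent, has 99% specificity and loses no true positives (assumptions), 97.5 false positives become 97.5 × 0.01, about 1, and the true share rises from 72% to 99.6% at 250 infected.
2. For each Period 1 serology positive, run the stored entry sample with the same anti-N assay and exclude those already positive from the Period 1 and pooled analyses.
3. Restate the sentence in Section 8.4.8 as a statement about sampling coverage, subject to assay accuracy.

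The cost is a few sentences and limited retesting of stored samples. A few true infections with weak antibody will drop out of the confirmed-only analysis.
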